## Abstract

**Background:**

Many countries today are undergoing a paradigm shift in mental health policies towards a recovery-oriented and rights-based approach. From this perspective, self-determination and self-management are fundamental factors for recovery. Despite this shift, there is still a lack of evidence on the effectiveness of training programmes aimed at promoting self-determination and self-management in recovery processes implemented in southern European or Spanish-speaking countries. The aim of this paper is to present a study protocol that evaluates the effectiveness of a 12-session recovery workshop implemented in community mental health services in Catalonia (Spain).

**Methods/design:**

This is a 12-week follow-up multi-centre non-randomized controlled trial design. At least 160 users will be recruited from 13 Community Rehabilitation Services (CRS) in Catalonia. Eligible participants are adult (≥ 18 years old) users of a CRS, who sign a written consent to participate. The experimental group participates in a recovery workshop, in which people learn to develop and implement their own plan of personal recovery, which includes a Wellness Toolbox, a Maintenance Toolkit, a Personal Growth Plan, a Mirror of Relapses, a Crisis Plan, and a Learning Agenda. The control group participates in the usual activities of the CRS. Data is collected using a questionnaire of sociodemographic characteristics, personal recovery, empowerment, hope and perceived social support. The users’ measurements are taken at the baseline and one week after the end of the workshop. The primary outcome measures include the Self-Identified Stage of Recovery and the Maryland Assessment of Recovery in Serious Mental Illness Scale (short version). The secondary outcome measures include the Netherlands Empowerment List, Dispositional Hope Scale, and Multidimensional Scale of Perceived Social Support. Descriptive statistics for characterizing the sample size will be performed. Multivariate analyses for repeated measures designs will be used to evaluate the primary and secondary outcomes. Between-group and within-subject comparisons will be conducted.

**Discussion:**

The results of the study will provide information on the usefulness of recovery workshops in a Mediterranean cultural context. Additionally, if this workshop is effective, it will be proposed for inclusion within the portfolio of community mental health services in Catalonia.

**Trial Registration:**

ISRCTN11695542 (Registration date: 5 July 2022).

**Supplementary Information:**

The online version contains supplementary material available at 10.1186/s12888-022-04350-y.

## Background

Currently, public mental health policies in many countries around the world promote recovery-oriented care, an approach whose main objective is to help people to have a meaningful and satisfying life, in accordance with their own preferences and values, beyond the presence or absence of symptoms [1–3]. Meeting this goal presupposes that people are allowed to make their own decisions. In this respect, self-determination [4–6] and exercising citizenship rights [7] have been both identified as conditions for the possibility of personal recovery. According to this idea, mental health service providers have a responsibility to promote self-determination, providing people with the tools they need to direct their own recovery processes, making their own decisions [8].

In 2002, Connecticut (USA) was the first state mental health authority in the United States to adopt a policy aimed at promoting a recovery-oriented system of care [9]. Within a few years, a trend towards pro-recovery policies spread throughout the whole United States, and to Scotland, first, and then to the rest of the United Kingdom [10]. This mental health policy shift was replicated in most anglophone countries [11] and in northern Europe [12] over the course of the first decade of this century and, more recently, in some countries insouthern Europe, such as Italy [13] and Spain [14]. Gradually, more and more countries around the world are adopting a recovery-oriented approach, driven by the QualityRights initiative of the World Health Organization [15]. WHO QualityRights is a strategic line and a toolkit designed to “improve service delivery in line with a person-centred, recovery and human rights-based approach” (WHO, p.80) [16].

In Spain, the administration of the health system is overseen by the Autonomous Communities (Spanish regions with their own government). In this regard, Catalonia, one of the 17 regions of Spain, introduced the recovery-oriented and rights-based approach to care in its strategic plans in 2017 [17, 18], promoting the deployment of a whole series of initiatives aimed at generating a change in the model of mental health care. One such initiative is the *Activa’t per la Salut Mental* programme (Get Active for Mental Health) [19], developed jointly by the Mental Health Services Administration, relatives’ and users’ organizations, and survivors’ movements. The aim of the programme is to encourage and enable people with mental health problems and their families to become active health agents in their recovery processes.

Within the framework of this programme, a new recovery tool has been designed and developed based on the principles and objectives of recovery-oriented approaches. This tool has two components: the Manual for the Recovery and Self-Management of Well-Being [20] and the Personal Workbook [21], developed through a participatory process (in which around 300 people took part) using a mixed methodology. A workshop has also been designed to enable participants to use the tool effectively [22]. It is now necessary to evaluate the effectiveness of this training program and the materials in order to be able to promote their use in mental health services and associative movements.

A little over a decade ago, Silverstein and Bellack (2008) summarized twenty years of research on recovery, identifying four areas of research and development: (a) the definition of recovery; (b) the development of reliable measures of recovery; (c) rates of and barriers to recovery; and (d) the effectiveness of recovery-oriented care [23]. Nine years after that publication, Leonhart et al. (2017) found that, even though the volume of work on personal recovery had significantly increased, there are still big gaps needing further research [24]. One of these gaps is how the intervention programmes aimed at promoting personal recovery are being implemented and evaluated.

Filling this gap is particularly necessary in non-anglophone countries, in which very little research has been conducted on this topic. A recent scoping review found that, out of 37 published studies aimed at evaluating the effectiveness of a recovery workshop, only 7 had been conducted in non-English speaking countries, and all of these were in Asia (three in Palestine and the others in China, Korea, Japan and Pakistan) [25]. More significantly, one of these studies found no improvements for most of the variables evaluated after the intervention [26]. Likewise, only three studies focused on exploring the applicability of one of these tools, the Wellness Recovery Action Plan (WRAP) [27], for an ethnic minority [28–30], with two of them concluding that it is necessary to adapt this recovery tool to incorporate a critical analysis of oppression and a gender perspective in the workshops [29, 30].

In short, the review of previous literature highlights the need to analyse the applicability and evaluate the efficacy of this type of intervention in other cultural contexts because, to date, “most of the studies were conducted in high-income countries, with a recovery-oriented mental health system, in which there are well-established networks of users and survivors, and an Anglo-Saxon/Protestant cultural background that highlights individual freedom and self-determination” (Sampietro et al., p. 9) [25].

In this article, we present the study protocol of a non-randomized controlled trial designed to evaluate the effectiveness of the recovery workshop of the *Activa’t per la Salut Mental* programme, implemented in mental health community services in Catalonia, Spain.

The main objective of the study is to evaluate if the recovery workshop of the *Activa’t per la Salut Mental* programme has an impact in terms of an improvement in personal recovery. The secondary objective is to evaluate the changes in the level of empowerment, hope and perceived social support among participants of the recovery workshop of the *Activa’t per la Salut Mental* programme.

The primary hypothesis to be tested is that participants in the experimental groups (i.e., users of a 12-week recovery workshop implemented in mental health community rehabilitation services) will improve their personal recovery more than the participants in the control group (i.e., users of the standard activities of the mental health community rehabilitation services) immediately one week after the intervention.

The secondary hypothesis to be tested is that the participants in the experimental groups (i.e., users of a 12-week recovery workshop implemented in community rehabilitation services) will improve their empowerment, hope, and perceived social support more than the participants in the control group (i.e., users of the standard activities of the community rehabilitation services) immediately one week after the intervention.

## Method

This protocol has been drafted following the Standard Protocol Items: Recommendations for Interventional Trials (SPIRIT) Statement, for reporting a clinical trial protocol [31] (see Additional file 1 for checklist). This is the first published version of the protocol.

### Study design

This is a multi-centre non-randomized controlled trial comparing users of community mental health services who participate in a 12-week recovery workshop to users who do not.

This study is part of a biggest project entitled “Toward recovery in people diagnosed with a severe mental disorder: Definition, assessment and intervention (RECO-DAI)”.

### Study setting and CRS enrolment

The study is conducted in 13 mental health Community Rehabilitation Services (CRS), spread over 75% of the territory of Catalonia. Both large cities (such as Barcelona, with more than 1.6 million inhabitants) and small municipalities (such as Amposta, with just 20,000 inhabitants) have been included. A CRS is a free, public mental health care resource with the aim of comprehensively accompanying people throughout their own recovery process. They offer specialized care designed to promote functional recovery, strengthen psychosocial skills and facilitate people’s inclusion in the community.

The CRS enrolment was conducted eight months before users’ recruitment. Mental health service providers in Catalonia that had previously collaborated with the *Activa’t per la Salut Mental* programme were invited to participate. Together, these 13 CRS offer community mental health services to a region with a total population of 1,700,000 people.

Prior to the study, from 16 April to 5 October 2021, at least two professionals from each CRS received 20.5 h of training on: (a) what personal recovery is and how to promote it; (b) how to draft their own personal recovery plan (with the new materials created in Catalonia) [20, 21]; (c) how to implement the recovery workshop of the *Activa’t per la Salut Mental* programme [22]; and (d) how to evaluate this recovery workshop (including instruments and study design).

### Eligibility criteria and recruitment

Eligible participants are adults who take part in the activities of a CRS, and who consent to participate in the study. There are 15 potentially eligible CRS whose professionals had previously attended the recovery workshop training course for trainers. Of these, only the CRS that have agreed to participate in the research, allow accessibility, and commit to the continuity of the project have been or will be involved in this study.

The inclusion criteria for participants are: (a) aged over 18 years and under 65 years; (b) user of a CRS; and (c) signature of the informed consent and commitment to participate. The exclusion criteria are: (a) presence of relevant cognitive impairment and comprehension difficulties; and (b) presence of severe or decompensated somatic disease.

The CRS professionals oversee the recruitment, offering all users of the service meeting the inclusion criteria the option of participating in an evaluated recovery workshop as part of the range of activities offered by the service. All users interested in participating can sign up, up to the maximum capacity of 10 participants. If the maximum capacity of workshop participants is exceeded, the last people signed up will remain on a waiting list for future cycles of the workshop. This is the standard procedure for all regular CRS activities. For the control group, the CRS professionals will follow the same procedure. If there are more than 10 people interested in participating in the control group, the CRS professionals will carry out intentional sampling, taking into account the demographic variables (age, sex, level of education, etc.) of the experimental group, to form a relatively equivalent group with respect to these variables.

All users interested in participating in the study are invited to a session prior to the start of the workshop, in which the research team resolves any possible doubts about the study’s aim and procedures. Their written informed consent is also obtained in this session.

CRS professionals assign an alphanumeric code to all trial participants, both in the experimental group and in the control group. The members of the research team do not have access to the information related to the group to which the participants belong until the interpretation phase of the collected and processed data.

The recruitment period ran from January to October 2022.

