Moreover, a distinctive feature of the Workshop is that not only is it a space for learning and reflection in relation to these contents, but also that it has a practical orientation. People who complete the recovery workshop are expected to have developed their own Recovery and Self-Management of Well-Being Plan, progressing through and completing their Personal Workbook in collaboration with their environment and professional care resources.

The learning objectives and specific content of each session can be found in the Guide for Implementing the Workshops with the Manual for Recovery and Self-Management of Well-Being [22].

The recovery workshop is implemented by CRS professionals, who have previously participated in 20.5 h of training on: (a) the principles of recovery-oriented care; (b) the materials from the *Activa’t per la Salut Mental* recovery workshop; (c) the contents and activities of the Recovery Workshop; and (d) the design of the evaluation of the effectiveness of the recovery workshop study. Additionally, in sessions fifth and tenth of the workshop, experts with experience in the recovery process (users and survivors) participate as trainers. In the fifth session, they share a life story of recovery and, in the tenth session, they explain what participating in a space of mutual support has given them in terms of their recovery process. They also present the network of mutual support that the participants have within their reach.

For their part, the members of the control group participate in the usual CRS activities. These activities include development of cognitive, communication and emotional skills workshops; leisure and free times activities; strengthening of social relationships; training and guidance for job placement; etc. For the most part, these activities take place on a weekly basis or more frequently.

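### At services with more than 10 control volunteers, staff choose the controls by discretionary sampling; a random draw within coarse demographic strata would serve the same aim without staff discretion

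*Protocol article*

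**What the plan says.** All references are to the protocol article.

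- **Recruitment.** Under Eligibility criteria and recruitment, "The CRS professionals oversee the recruitment".
- **Workshop arm.** It is filled by sign-up to a cap of 10. Beyond that, "the last people signed up will remain on a waiting list for future cycles of the workshop".
- **Control arm.** The same procedure is said to apply, but with an exception. "If there are more than 10 people interested in participating in the control group", then "the CRS professionals will carry out intentional sampling, taking into account the demographic variables" of the workshop group. The examples are age, sex and education, followed by an open-ended etc. The aim is "to form a relatively equivalent group with respect to these variables".
- **Delivery.** Under Intervention, "The recovery workshop is implemented by CRS professionals". Under Study setting and CRS enrolment, at least two professionals per CRS were trained, and one of the topics was "how to evaluate this recovery workshop (including instruments and study design".
- **Masking.** Only the research team is kept from knowing group membership, until results are interpreted. The CRS professionals assign the participant codes in both groups.
- **Limitations.** The Discussion explains the lack of randomisation by small services with too few interested users, and admits that the arms differ in interest in the workshop. It does not mention selection of controls by staff.

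**The concern.** The article states a selection method here, so this is not detail left to a fuller document. Followed exactly, the method lets staff choose among volunteers whom they may know, in one arm only. Staff may be aware of motivation, current stability or likely attendance, none of which is among the listed sociodemographic data. If such knowledge influences the choice, the expected change in the control arm moves. Adjustment for demographics or baseline scores cannot fully undo that, because the choice operates among people who look alike on those variables.

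The stated purpose, demographic similarity, does not need personal choice. The reason given for not randomising between arms, a shortage of interested users, does not apply to choosing among surplus control volunteers.

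**Working it through.** The article gives no figure for this step, so there is none to reproduce. The first check sets the rules side by side; the second gives an illustration of scale.

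**1. The two rules for an oversubscribed group**

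| | Workshop arm | Control arm |
|---|---|---|
| Cap | 10 | 10 |
| Who is kept | earliest to sign up | those chosen by CRS professionals |
| Criterion | order | open demographic list, approximate equivalence |
| Discretion | none in who is kept | yes, among all sets that satisfy the criterion |

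Order of sign-up is not random either, but it leaves staff no choice. With a random draw within strata, the expected shift caused by the selection step is zero, given the volunteers and the strata. With intentional sampling, nothing in the text bounds it.

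**2. How often the rule could apply**

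Inputs: 160 users (Sample size; a minimum according to the Abstract) and 13 CRS. Equal arms are assumed.

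- Controls: 160 / 2 = 80.
- Average per CRS: 80 / 13 = 6.2, below the cap of 10.
- 25% of controls from oversubscribed CRS is 20 people, or 2 CRS at the cap. 50% is 40 people, or 4 CRS.
- 100% would need 80 / 10 = 8 CRS at the cap and no controls from the other 5.

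**3. Illustrative size**

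Assumptions: staff choice shifts the expected change of the affected controls by 0.20 SD, always in the same direction; observations are independent. Neither the shift nor the share of controls affected comes from the article.

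- Completers per arm at 25% attrition: 160 × 0.75 / 2 = 60.
- Bias = share × 0.20 SD: 0.25 × 0.20 = 0.05 SD and 0.50 × 0.20 = 0.10 SD.
- Noncentrality = bias × √(60/2): 0.05 × 5.48 = 0.27 and 0.10 × 5.48 = 0.55.
- Rejection probability of a two-sided 5% test with no true effect (noncentral t): 0.058 and 0.084.

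**4. Is 0.20 SD a possible value?**

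Take the extreme in which staff always choose the 10 volunteers with the poorest perceived prognosis out of M, and perceived prognosis correlates r with change. For r from 0.1 to 0.5, the simulated shift in the control mean is:

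- M = 12: 0.03 to 0.14 SD
- M = 15: 0.05 to 0.26 SD
- M = 20: 0.08 to 0.38 SD

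M and r are assumptions, and demographic matching would limit the shift. Choosing the best-prognosis volunteers would reverse its sign. So 0.20 SD lies inside a worst-case range and is not a central estimate.

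**The case against.** The case on the other side has several parts, and much of it stands.

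- **The rule may seldom apply.** With about 6 controls per CRS on average and some small services, oversubscription may be uncommon. This stands. The article does not say how many CRS are affected, and 160 is a minimum.
- **The direction is unknown.** This also stands. Staff at different services could err in different ways, and a consistent shift is an assumption.
- **The text names only demographic criteria.** The open end of the list may simply refer to the sociodemographic variables given elsewhere, and an article may leave a matching algorithm to the full protocol. That is fair as to the missing detail. It does not change the stated choice of intentional over random sampling.
- **The larger bias is already disclosed.** Interest in the workshop separates the arms, and no draw among control volunteers makes them exchangeable. True, but staff selection is a separate component, undisclosed and avoidable.
- **A draw has practical limits.** Two sexes by two age bands by three education levels gives 2 × 2 × 3 = 12 cells for 10 places, which is too fine. A draw by the research team would also breach its masking. Both points constrain the remedy.

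A reader might go further and infer that workshop leaders with an interest in the result pick their own comparators. The documents do not support that: they give both tasks to one staff role, do not say the individuals are the same, and describe no prognostic criterion. A reader might also extend the illustration to all controls (bias 0.20 SD, rejection about 19%). That requires 8 services at the cap, none elsewhere and the same error at each, which fits the plan poorly.

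**Conclusion.** The point holds as a limited, conditional weakness. At any CRS with more than 10 control volunteers, the prescribed procedure leaves room for unrecorded prognosis or staff expectation to influence who becomes a control, while the workshop arm has no such discretion. It is a risk, not a demonstrated bias. Its direction is unknown and the number of services concerned is not stated.

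The figures of 0.05 to 0.10 SD and a type I error of about 6% to 8% are an illustration only. They rest on an assumed consistent shift of 0.20 SD in 25% to 50% of controls. The change is worth making because it is cheap and meets the article's own aim, not because the bias is known to be large.

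**What to change.** **For any control selection still to come.** Replace intentional sampling at oversubscribed CRS with a random draw:

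1. List all eligible control volunteers by code.
2. Fix a few coarse strata in advance, for example sex by two age bands, with a rule for collapsing them when sparse.
3. Draw within strata in proportion to the workshop group at that CRS.
4. Use a pre-generated random order applied at the CRS, or have someone outside the masked research team make the draw, so that the team's masking is kept.
5. Record the numbers of volunteers and of people drawn at each CRS.

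**For controls already chosen.** The article reports that recruitment ran from January to October 2022, so this may be most of them. Flag each CRS where intentional sampling was used and report volunteers against those selected. Add staff selection to the limitations, beside self-selection. Pre-specify a sensitivity analysis without those CRS.

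**Cost.** The draw needs one paragraph of procedure and a short list per oversubscribed CRS, with no extra participants or assessments. Demographic balance may be slightly looser than under deliberate choice, which covariate adjustment can absorb. The sensitivity analysis loses precision: if both arms lost 25% to 50% of participants, standard errors would grow by a factor of 1/√0.75 = 1.15 to 1/√0.50 = 1.41. It should therefore support the main analysis, not replace it.
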